### Participant timeline {13}

Participant timeline is shown in Fig. 2.

**Fig. 2 Fig2:**
[figure not shown]
Participant time line showing the patient contacts in the study: randomization, intervention and follow-up

### Sample size {14}

One hundred twenty patients will be included, 60 patients in each group. The sample size calculation is based on a clinical relevant difference of 10 point in KOOS4, a standard deviation (SD) of 15 and power of 0.90 (two sided). Ninety-eight patients are required; due to the risk of dropout, 120 patients will be included, 60 in each group. The used SD and clinically relevant difference are recommended at KOOS.nu.

### Recruitment {15}

Participants are recruited from the arthroplasty and sports surgery departments of each hospital. Both departments have many patient contacts, which will give a continuous enrolment of possible participants.

## Assignment of interventions: allocation

### Sequence generation {16a}

Randomization is computer based, performed in blocks of twelve and is following the random allocation rule to ensure balanced group sizes. Patients are allocated 1:1 to either the control or the intervention group.

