**Fig. 1 Fig1:**
[figure not shown]
Patient flow diagram. Patients assessed for eligibility are registered according to the consort requirements and will be presented in the final study paper in a consort flow diagram like this

All patients assessed by the primary investigator for eligibility are registered according to the consort requirements.

If a patient meets the inclusion criteria, and has signed the declaration of consent, baseline registration is recorded by the treating surgeon in a REDcap database designed specifically for the study. After recording baseline data, a survey is automatically sent to the patient by email. The survey includes baseline KOOS4, Tegner activity score and questions regarding work status.

The inclusion criteria are as follows:
* Age 18–70 years.* Kellgren-Lawrence score grades 2–3 in the tibiofemoral joint, either in the * medial, lateral or both compartments.* The patient must be expected to be able to attend follow-up examinations.* The patient must be able to speak and understand Danish.* The patient must be able to give informed consent.

Exclusion criteria are:
* Smoking (the patient must consent to being non-smoking 6 weeks before and 6 weeks after the procedure)* Varus or valgus malalignment of the knee > 5°* Laxity of the medial collateral ligament (MCL) or lateral collateral ligament (LCL) of 10° or more compared to the opposite knee* Knee instability and anterior-posterior laxity of 3 mm or above (compared to the opposite knee)* Preceding open surgery to the knee or fracture in the proximal tibia or distal femur* Extension deficit of the knee* Kellgren-Lawrence score grade 4 in any of the three compartments* BMI > 40* Terminal illness or severe medical illness: ASA score higher than or equal to 3

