### Concealment mechanism {16b}

Two researchers with no other connection to the trial is responsible for packing of continuously numbered, sealed, opaque envelopes. The allocation key is stored by and only accessible by the researcher who generated the allocation key. If a participant needs to know the allocated treatment ahead of trial termination, the study nurse will arrange this. Patients are still followed up according to the intention to treat principle.

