## Assignment of interventions: blinding

### Who will be blinded {17a}

Blinding of the patient is secured as follows: The liposuction and micro-fragmentation of the fatty tissue is performed in the operating theatre. When the graft is ready for use, two 5-ml syringes containing active treatment and two 5-ml syringes containing saline are prepared.

The randomization envelope is opened by the treating surgeon, who is not blinded to the intervention.

The patient as well as the scrub nurse is blinded to the treatment. Both are visually shielded by the surgical drapes. Before opening the randomization envelope, the patient is informed that after opening of the envelope there is no further communication with the treating surgeon. The surgeon is silent once the randomization has taken place to limit subliminal bias. After the intra-articular injection of either micro-fragmented fat or saline, the surgeon empties the remaining syringes in order to conceal the given treatment.

Injection is performed with a 21G cannula. Due to the difference in viscosity of the graft and saline, the treating surgeon cannot be blinded.

In order to investigate if the blinding is working, the patients will be asked at 6 months’ follow-up which group he/she believes he/she was assigned to.

The data assessment is blinded as the data analysts are blinded.

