### Data management {19}

#### Data collection methods

Study data are collected and managed using REDCap electronic data capture tools hosted at the capital region of Denmark [27, 28].. REDCap (Research Electronic Data Capture) is a secure, web-based software platform designed to support data capture for research studies.

Baseline data about the patient is entered by the investigating surgeon. Data is entered directly in the database, ensuring secure storage of data and reducing the risks of typing errors, double data entry, data entry for a wrong patient, etc.

Information about the procedure including any complications is recorded by the treating surgeon in the REDcap database and level of pain during surgery is entered by the treating surgeon. The patient scores his/hers pain level on a visual analogue pain scale immediately after the surgery.

Data entry activates automated surveys to be sent to the patient at 3, 6, 12 and 24 months after the surgery. The patient will receive a link to the surveys by email and is contacted by phone by a study nurse to ensure completeness of the follow-up. The study nurse did not take part in the surgery and is blinded to the randomization. See Fig. 3 for the study timeline.

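### One constant block length of twelve, with numbered envelopes opened by an unblinded surgeon, lets at most about 14% of allocations be deduced in advance

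*Protocol article*

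**What the plan says.** Sequence generation {16a} fixes a single block length and the ratio: "Randomization is computer based, performed in blocks of twelve and is following the random allocation rule to ensure balanced group sizes", and "Patients are allocated 1:1 to either the control or the intervention group". Concealment mechanism {16b} uses "continuously numbered, sealed, opaque envelopes", packed by two researchers who have no other part in the trial. It adds: "The allocation key is stored by and only accessible by the researcher who generated the allocation key". Implementation {16c} gives generation of the key to an independent senior researcher.

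Under Who will be blinded {17a}: "The randomization envelope is opened by the treating surgeon, who is not blinded to the intervention". The same section gives the reason: "Due to the difference in viscosity of the graft and saline, the treating surgeon cannot be blinded". The envelope is opened after the fat has been harvested and both sets of syringes are ready.

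On entry to the trial, Eligibility criteria {10} states that once a patient meets the criteria and has consented, "baseline registration is recorded by the treating surgeon in a REDcap database designed specifically for the study". Data collection methods, under Data management {19}, says: "Baseline data about the patient is entered by the investigating surgeon". Who will take informed consent? {26a} has an arthroplasty or sports surgeon make the first judgement of suitability, and the primary investigator assess every patient for eligibility. Study setting {9} names two centres.

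**The concern.** Sealed, opaque envelopes and a locked key stop anyone from reading the next allocation. They do not stop anyone from inferring it from envelopes already opened. Three stated features together make that inference possible: the block length is constant and printed in the protocol, the envelopes form a numbered series, and the person who opens each one learns what was given. Once six patients in a block have received the same treatment, every remaining patient in that block must receive the other.

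If someone who can foresee an allocation also influences who is referred, who is enrolled or in what order patients are treated, the groups can come to differ at baseline without any intent. The primary outcome, KOOS4 at 6 months, is reported by the patient. A difference in the kind of patient entering each arm would carry into the comparison, and analysis cannot reliably repair it afterwards.

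**Working it through.** The plan gives no figure for predictability, so there is none to reproduce.

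**Inputs.** Block length 12 and ratio 1:1, so 6 + 6 per block (Sequence generation {16a}). Total 120 patients (Sample size {14}), so 120/12 = 10 complete blocks. Two centres (Study setting {9}). The number of treating surgeons, and whether the centres share a list, are not stated. Section {16a} names both blocks and the random allocation rule; I read this as the rule applied within each block, which amounts to permuted blocks.

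**Case A: the observer knows the block length and every earlier allocation in the block.**

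The allocation at position k is certain if one arm has already used its six places. The probability is 2 × C(k−1, 6) / C(12, 6), with C(12, 6) = 924.

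| Position k | Probability that it is certain |
|---|---|
| 1 to 6 | 0 |
| 7 | 2/924 = 0.002 |
| 8 | 14/924 = 0.015 |
| 9 | 56/924 = 0.061 |
| 10 | 168/924 = 0.182 |
| 11 | 420/924 = 0.455 |
| 12 | 924/924 = 1 |

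The sum is 1584/924 = 12/7 = 1.714 per block. The general form is 2m/(m+1) with m = 6. As a share this is 1.714/12 = 14.3%; over ten blocks it is 17.1 of 120 patients. Enumerating all 924 sequences gives the same result.

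Guessing the arm that is behind, and tossing a coin when the arms are level, is right in a share [m + (4^m/C(2m, m) − 1)/2]/(2m). With m = 6: 4096/924 = 4.433; (4.433 − 1)/2 = 1.716; (6 + 1.716)/12 = 64.3%, against 50% by chance.

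**Case B: one list shared by two centres.** Assume patients come 50:50 in random order and the surgeon knows only own-site allocations. By simulation, about 0.2% of that surgeon's patients are certain in advance. Guessing the lagging arm is right about 56% of the time if the block boundaries are known, and about 53% from a running tally alone.

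**After a change to random block lengths of 8, 12 and 16**, on a fully observed list with lengths undisclosed (simulation): certain allocations are about 1.5%, or 0.015 × 120 = about 2 patients. Guessing the lagging arm stays at about 64%, because it needs only a running tally and not the block length.

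**For scale.** Smaller fixed blocks are worse: a block of 4 gives 33% certain and 71% correct guesses. One unblocked random allocation rule over all 120 would give 2.0 certain allocations (1.6%) and 55.3% correct guesses.

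**The case against.** The strongest reply has four parts.

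- **Control over inclusion.** A reader might infer that the treating surgeon chooses or schedules the patients. The text does not say so. The surgeon records baseline data after eligibility and consent, and the primary investigator assesses eligibility. Whether that investigator also treats is not stated. This stands: the documents show an opportunity, not a demonstrated route. Because the envelope is opened only when the graft is ready, dropping a patient after opening is not the risk.
- **Size.** A reader might take 14% and 64% as estimates. They need one person to see a whole series. With a shared list and own-site knowledge, certainty nearly vanishes. This also stands, so the figures are upper bounds.
- **Safeguards.** Twelve is already a fairly large block, and the generator and packers are independent. That is to the plan's credit, but none of it prevents deduction from opened envelopes when the length is fixed and known.
- **Centres.** A reader might conclude that the plan is wrong not to stratify by centre, or not to put centre in the primary model. The article does not support that. Such details are commonly left to the full protocol or analysis plan, which are not shown, and a 1:1 trial does not require stratification by centre.

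It is also an inference that surgeons knew the block length and that envelopes remained unopened. The article prints the length and, in the caption to Fig. 3, describes recruitment as expected to end in November 2021, but its publication date is not shown.

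**Conclusion.** The point holds as a modest weakness in a stated design choice. With a constant, known block of twelve, between about 0.2% and 14% of allocations can be deduced with certainty (at most about 17 of 120). The upper end assumes that a surgeon knows the block length and sees a complete series, as with one list per centre and one treating surgeon, or surgeons who share what they know. The lower end assumes one list split equally between the centres, with no exchange of information. The article does not say which arrangement applies. Nothing in it shows that selection occurred. It is worth correcting because the feature is avoidable and the change is cheap, not because the trial's conclusions can be said to be in doubt.

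**What to change.** For envelopes not yet opened, have the independent researcher generate the remaining sequence with block lengths drawn at random from fairly large sizes, for example 8, 12 and 16. Withhold the lengths from surgeons and enrolling staff, including in the documents they hold.

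Keep the present list structure across centres. If the list is now shared, splitting it would hand each site a complete series and raise lagging-arm guessing from about 53–56% to about 64%. Do not move to small blocks, which make prediction easier.

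The article should also state whether the list is shared or separate by centre, whether the primary investigator also treats, and what the random allocation rule means within blocks of twelve.

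The cost is one new sequence and repacking of the remaining envelopes by the same independent researchers, with a possible slight imbalance in final group sizes. The gain is limited to certain predictions; the lagging-arm guess rate does not improve.

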### Concealment mechanism {16b}

Two researchers with no other connection to the trial is responsible for packing of continuously numbered, sealed, opaque envelopes. The allocation key is stored by and only accessible by the researcher who generated the allocation key. If a participant needs to know the allocated treatment ahead of trial termination, the study nurse will arrange this. Patients are still followed up according to the intention to treat principle.

### Implementation {16c}

An experienced senior researcher with no other connection to the trial is responsible for generation of the allocation key.

## Assignment of interventions: blinding

### Who will be blinded {17a}

Blinding of the patient is secured as follows: The liposuction and micro-fragmentation of the fatty tissue is performed in the operating theatre. When the graft is ready for use, two 5-ml syringes containing active treatment and two 5-ml syringes containing saline are prepared.

The randomization envelope is opened by the treating surgeon, who is not blinded to the intervention.

The patient as well as the scrub nurse is blinded to the treatment. Both are visually shielded by the surgical drapes. Before opening the randomization envelope, the patient is informed that after opening of the envelope there is no further communication with the treating surgeon. The surgeon is silent once the randomization has taken place to limit subliminal bias. After the intra-articular injection of either micro-fragmented fat or saline, the surgeon empties the remaining syringes in order to conceal the given treatment.

Injection is performed with a 21G cannula. Due to the difference in viscosity of the graft and saline, the treating surgeon cannot be blinded.

In order to investigate if the blinding is working, the patients will be asked at 6 months’ follow-up which group he/she believes he/she was assigned to.

The data assessment is blinded as the data analysts are blinded.

### Procedure for unblinding if needed {17b}

The participants can ask to be unblinded upon request. The project manager will ask the person responsible for generation of the allocation key. The person has no other connection to the study.

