**Discussion:**

This trial is the first to investigate the efficacy of autologous, micro-fragmented adipose tissue in a randomized controlled trial. The study uses the patient-reported outcome measure Knee Injury and Osteoarthritis Outcome Score (KOOS4) after 6 months as the primary outcome, as it is believed to be a valid measure to assess the patient’s opinion about their knee and associated problems when suffering from osteoarthritis.

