### Plans to promote participant retention and complete follow-up {18b}

The study nurse will be responsible for follow-up. The database will show if the participants have completed the questionnaires. If the questionnaire is not completed, the study nurse will make a phone call to the participant.

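### Unblinding on request has no stated limit before the self-scored 6-month KOOS4, and the two sections that govern it differ on condition and route

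*Protocol article*

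**What the plan says.** Two sections of the protocol article govern disclosure of the allocation to a participant.

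- Procedure for unblinding if needed {17b}: "The participants can ask to be unblinded upon request". On the route: "The project manager will ask the person responsible for generation of the allocation key". No time limit is given.
- Concealment mechanism {16b}: "If a participant needs to know the allocated treatment ahead of trial termination, the study nurse will arrange this". It adds: "Patients are still followed up according to the intention to treat principle". On custody of the key: "The allocation key is stored by and only accessible by the researcher who generated the allocation key".

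Three other places bear on this. Data collection methods (under {19}) says of the nurse: "The study nurse did not take part in the surgery and is blinded to the randomization". The retention section {18b} says: "The study nurse will be responsible for follow-up", and has the nurse telephone participants whose questionnaires are incomplete. The abstract's Discussion states: "The study uses the patient-reported outcome measure Knee Injury and Osteoarthritis Outcome Score (KOOS4) after 6 months as the primary outcome".

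The only check on blinding is in {17a}: at 6 months participants are asked which group they think they were in.

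**The concern.** KOOS4 has no assessor other than the participant. Blinding of the primary outcome is therefore blinding of the participant, and {17a} goes to some length to secure it: fat is harvested and processed before the envelope is opened, both sets of syringes are prepared, the drapes shield the patient's view, and the surgeon stays silent. A participant who is told the allocation before the 6-month questionnaire loses that protection, and knowing it was saline or fat can move a subjective score.

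The rule that allows this is stated in the article, so it is not a detail left to a fuller document. Because {16b} speaks of disclosure before the trial ends, {17b} cannot safely be read as covering only end-of-study disclosure.

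The second issue is the procedure. The sections name different people to handle a request, and one of them is the nurse who is described as blinded and who stays in contact with participants during follow-up. If the nurse learns allocations while handling requests, a further layer of blinding is weakened.

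**Working it through.** **Step 1. Compare the sections.**

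| Item | {16b} | {17b} |
|---|---|---|
| Condition | the participant needs to know | the participant asks |
| Timing | before the trial ends | not stated |
| Who handles it | study nurse | project manager, who asks the key holder |
| Protection of the 6-month KOOS4 | none | none |

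The condition and the person handling the request differ. Neither section refers to the primary outcome time point. The nurse's blinded status in the data collection section sits awkwardly with the role given in {16b}, but {16b} also restricts the key to the person who generated it. Arranging a disclosure therefore does not by itself mean learning the allocation.

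**Step 2. Reproduce the plan's figure, to fix the scale.** The inputs are a difference of 10, SD 15 and power 0.90 (Sample size {14}), and a two-sided 5% level ({20a}).

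- Normal approximation: n per arm = 2 × (1.96 + 1.28)² × (15/10)² ≈ 47.3, rounded up to 48, or 96 in total.
- Two-sample t-test: power is 0.898 at 48 per arm and 0.904 at 49, so 49 per arm, or 98 in total.

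The stated 98 reproduces. The standard error of the difference at 49 per arm is 15 × √(2/49) ≈ 3.03 points.

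**Step 3. Illustrate the possible bias.** The document gives neither the share unblinded nor the size of any shift, so both are assumed here. Let a share f of each arm learn the allocation before 6 months, and let their scores shift by b points, up in the active arm and down in the control arm. The spurious difference is then 2 × f × b. If only controls shift, it is f × b. With no true effect, the probability of a significant result is 1 − Φ(1.96 − bias/3.03) + Φ(−1.96 − bias/3.03).

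| f per arm | b | Bias, both arms shift | Type I error | Bias, controls only | Type I error |
|---|---|---|---|---|---|
| 5% | 5 | 2 × 0.05 × 5 = 0.5 | 0.053 | 0.25 | 0.051 |
| 10% | 10 | 2 × 0.10 × 10 = 2.0 | 0.101 | 1.0 | 0.063 |
| 20% | 10 | 2 × 0.20 × 10 = 4.0 | 0.262 | 2.0 | 0.101 |

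With 60 randomised per arm, these shares are 3, 6 and 12 participants per arm. The error rates use the planning SD and a simple comparison of means. The planned mixed model would change them somewhat, but not the bias formula.

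**The case against.** The case against has several parts.

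- **The condition.** A reader might infer from {17b} that anyone can be unblinded at any time without a reason. The text does not establish that. It sits under a heading about unblinding if needed, and {16b} requires need. This stands: the fair statement is that the condition is worded inconsistently, not that none exists.
- **The nurse.** A reader might infer that the nurse is unblinded. The document does not show it, since only the generator can open the key. The two routes could also be one chain, in which the nurse receives the request and the project manager contacts the key holder. Participants complete the questionnaires themselves through an emailed link. This stands too: the nurse's blinding is at risk only.
- **The size.** No request rate is given, and at 5% and 5 points the effect is negligible. Equal and opposite shifts in both arms are the less favourable assumption. It is also tempting to say that dissatisfied participants would ask most, but nothing in the document supports this. Nor does the rule undo the theatre procedure for everyone: only those who are told lose blinding.
- **Existing safeguards.** Follow-up by intention to treat, blinded analysts and the 6-month treatment guess all help with something else. The first keeps unblinded participants in the analysis, the second protects the analysis, and the third measures belief. None removes reporting bias from a score given by someone who knows the allocation, and the guess as described does not separate those told from those guessing. This part of the objection fails.

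**Conclusion.** The point holds in a limited form. As written, the protocol lets a participant learn the allocation before scoring the primary outcome, under a condition and by a route on which {16b} and {17b} disagree, and nothing protects the 6-month KOOS4. Material bias is possible but not demonstrated. Under the assumed values it ranges from 0.5 to 4 points against a target of 10 (0.25 to 2 if only controls shift), and it is small if requests are rare. Nothing in the protocol keeps them rare, and bias in a score already reported cannot be removed afterwards. This is a cheap improvement rather than a flaw shown to invalidate the primary comparison.

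**What to change.** 1. Reconcile {16b} and {17b} into one condition and one route: requests go from the project manager to the key holder, and the study nurse neither arranges the disclosure nor is told of it.
2. Defer discretionary requests until that participant's 6-month KOOS4 has been returned. The grounds for earlier disclosure are for the investigators to define. Deferral to the 24-month survey would also protect the later outcomes, but it is a debatable further step and is not needed for the primary outcome.
3. Record the date of each unblinding, and report by arm how many participants were unblinded before their 6-month KOOS4.
4. Add a sensitivity analysis for those participants. One option is to set scores given after unblinding to missing and apply the multiple imputation already planned in {20c}, under both missing-at-random and missing-not-at-random assumptions.

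Cost: some participants wait up to 6 months for an answer, and a few who are refused may withdraw, which exchanges possible reporting bias for missing data. The change also needs written notice to the ethics committee and participants under {25}, and the Fig. 3 caption shows that inclusion began in December 2018. For participants already past 6 months, only the recording, reporting and sensitivity analysis can still help the primary outcome.
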